## Advantages and Pitfalls

This study is a prospective, multicenter, and observational cohort study conducted in two centers in Germany. A disadvantage of our study is the short observation period of our subjects, which is currently limited to 3 months. The study cohort can only be examined at two different time points after the baseline visit. The effects of exacerbation at the longitudinal level cannot be determined yet. Therefore, we are currently planning to establish a longitudinal study with the wheezers to be able to observe the mechanisms behind their development of bronchial asthma in the FU. One consideration here, for example, would be the recruitment of children when being infected with viral infections (e.g., influenza virus, respiratory syncytial virus, or coronavirus). Biomaterials could be collected at different points in time, for example, during exacerbation and FU. In addition, a further pitfall is the reduced motivation of parents and patients to attend FU visits, as is the case in many studies. This presents a major problem to achieve a significant subject number.

A further limitation is a regional dependency during the interpretation of the results. Our study cohort will be recruited in two urban centers, and a comparison cohort living in rural areas is currently not included. Here, supra-regional study centers should be included in the near future. Subsequently, there are also country-specific difficulties in the interpretation of the observed data. Another limitation is the lack of recruitment of adult asthmatics. Although we can compare the data with healthy children and adolescents, we do not have any reliable information on age dependency. We are currently planning an adult cohort and hope to submit the ethics proposal in the foreseeable future.

To handle the sampling procedure homogenously, we established standard operating procedure protocols where each sample should be processed, standardized upon biomaterial collection to reduce the pitfalls between persons. All study relevant materials, e.g., monovettes, swab materials, etc., were tested for suitability before recruiting. The nucleic acid concentration and the cell counts were appropriated during pilot sample processing.

In contrast, there is a large number of advantages to the study. Briefly, there is little data in the literature on infants with chronic bronchitis and adolescents with asthma exacerbation. Questionnaires can be used to identify risk factors that may have potentially led to exacerbation. In addition, impulse oscillometry ensures first lung function volumes in children beyond the age of 2 years, which we additionally collect in the course of the study. Phenotype and endotype comparisons between wheezers and asthmatics can be done, and potential diagnostic and therapeutic schemes can be outlined. The experiments are currently being carried out with the latest technologies and the experimental results. The current biomaterial number of approximately 2.500 samples ensures accurate statistical analyses. Biomarker research is currently one of the most important areas in translational research. Here, we can lay the first foundations with complex experiments and verify their clinical applicability. The large study network from a total of 12 centers offers valid feasibility of the experiments.

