## Abstract

In summer 2017, the World Health Organization published 10 facts on asthma, which is known as a major non-communicable disease of high clinical and scientific importance with currently several hundred million people—with many children among them—suffering from air passages inflammation and narrowing. Importantly, the World Health Organization sees asthma as being underdiagnosed and undertreated. Consequently, much more efforts in clinical disease management and research need to be spent on reducing the asthma-related health burden. Particularly, for young approximately 6 months aged patients presenting recurrent bronchitic respiratory symptoms, many parents anxiously ask the doctors for risk prognosis for their children's future life. Therefore, we urgently need to reevaluate if the current diagnostic and treatment measures are in concordance with our yet incomplete knowledge of pathomechanisms on exacerbation. To contribute to this increasing concern worldwide, we established a multicentric pediatric exacerbation study network, still recruiting acute exacerbated asthmatics (children >6 years) and preschool asthmatics/wheezers (children <6 years) since winter 2018 in Germany. The current study that has a currently population comprising 176 study participants aims to discover novel holistic entry points for achieving a better understanding of the poorly understood plasticity of involved molecular pathways and to define biomarkers enabling improved diagnostics and therapeutics. With this study description, we want to present the study design, population, and few ongoing experiments for novel biomarker research.

**Clinical Trial Registration**: German Clinical Trials Register (Deutsches Register für Klinische Studien, DRKS): DRKS00015738.

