## Methods and Analysis

To counteract to this concern, we have built a clinically prospective, multicentered, observational exacerbation cohort to provide deeper insights. Starting in winter 2018, we have now established a pediatric exacerbation network in Germany. The study recruitment is currently ongoing, up to date having already recruited 176 study subjects having chronic bronchitis/wheezing episodes (age group <6 years, *n* = 62), children and adolescents with bronchial asthma (age group >6 years, *n* = 55) presenting recurrent asthma attacks, as well as healthy children, adolescents, and adults (*n* = 59). Currently, our biomaterial collection comprises approximately 2,500 specimens, including sera, plasma, cells, swabs, and sputum.

The study cohort comprises two diseased groups (acute exacerbated wheezers and asthmatics) and healthy children and adults. The subjects will not undergo any interventional/allergic provocations.

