The inclusion criteria for subjects with asthma are based on international recommendations, including lung function parameters (25), a gestational age over 37 weeks with an inconspicuous peripartal/postnatal period, and presenting an acute asthmatic attack at study enrollment. The definition of subjects with a wheeze is based on previously published data (26–29), including a history of at least two obstructive bronchitis episodes and acute wheezing at study enrollment, as well as an inconspicuous peripartal/postnatal period. Patients (chronic bronchitis and asthmatics) suffering from acute wheezing, respiratory illness, dyspnea, chest tightness, etc. (acute respiratory symptoms) were classified as “exacerbators.” The recruitment of wheezers is clinically and scientifically promising because underlying mechanisms of whether wheezers will develop chronic asthma are not sufficiently understood. Epigenetic signatures/environmental factors are likely to play important roles in disease development and persistence of symptoms (30, 31). We aim to analyze similarities between wheezers and asthmatics to make the diagnosis at the early stages of the disease and to discover potential biomarkers for the clinical routine. Moreover, subjects with no chronic diseases or chronic medication and an inconspicuous neonatal period were classified as healthy controls (age range: 3 months to 65 years of age). The healthy pediatric controls will be age- and sex-matched with diseased children (preschool asthmatics/wheezers and asthmatics). The recruitment of healthy adults will be helpful for correlation analyses of age-dependencies. In the future, we are also planning to include adult asthmatics. This is currently in consideration with the entire study members.

All individuals will be observed on the basis of two follow-up (FU) visits to recognize how the “active” and “non-active” phases are presented and differ, respectively (Figure 2).

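### Wheezers (<6 years) and asthmatics (>6 years) share no age, so differences found by comparing them directly cannot be attributed to disease rather than age

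*Protocol article*

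**What the plan says.** The Abstract describes recruitment of "acute exacerbated asthmatics (children >6 years) and preschool asthmatics/wheezers (children <6 years)". Methods and Analysis repeats the bands with counts: participants "having chronic bronchitis/wheezing episodes (age group <6 years, *n* = 62)", "children and adolescents with bronchial asthma (age group >6 years, *n* = 55)", "as well as healthy children, adolescents, and adults (*n* = 59)".

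The same section makes the comparison of the two diseased groups an aim: "We aim to analyze similarities between wheezers and asthmatics to make the diagnosis at the early stages of the disease", and to find biomarkers for routine use. Advantages and Pitfalls then states, without mentioning age: "Phenotype and endotype comparisons between wheezers and asthmatics can be done, and potential diagnostic and therapeutic schemes can be outlined".

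Methods and Analysis mentions age and sex matching twice, each time between diseased and healthy children. For group comparisons it names analysis of variance and customary significance tests, for two groups that it does not identify. Advantages and Pitfalls does concede a lack of reliable information on age dependency, but attributes it to the absence of adult asthmatics.

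**The concern.** Disease group is fixed by age. A marker that differs between wheezers and asthmatics may differ because of disease, because children mature, or both, and the direct contrast cannot say which. Conversely, an apparent similarity may be a disease effect offset by an age effect. The markers planned (cytokines, non-coding RNA, microbiome, lung function) could plausibly change during childhood.

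At stake is the aim of recognising asthma early from what wheezers and asthmatics have in common, and the diagnostic and therapeutic schemes the article expects from the comparison. The limitation it does state would not help: recruiting adult asthmatics creates no overlap between children under 6 and children over 6.

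**Working it through.** **Inputs from the article.** Wheezers: n = 62, under 6 years. Asthmatics: n = 55, over 6 years. Healthy participants: n = 59, children and adults together, with no split given. The stated total reproduces: 62 + 55 + 59 = 176. No mean ages, age trends, sample-size calculation or power figure are given.

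**Overlap.** The bands (<6) and (>6) have no age in common. This needs no assumption.

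**Illustration of size.** Assumptions: mean ages of about 3 and 11 years (gap 8), outcome SD 1, no disease difference, linear drift with age, two-sided 5% t-test.

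- Spurious difference = slope × gap.
- SE of the direct contrast = √(1/62 + 1/55) = √(0.01613 + 0.01818) = 0.185 SD.
- Non-centrality = spurious difference / 0.185, with 115 degrees of freedom.

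| Slope (SD/year) | Spurious difference (SD) | Non-centrality | Declared different |
|---|---|---|---|
| 0.02 | 0.16 | 0.86 | 14% |
| 0.05 | 0.40 | 2.16 | 57% |
| 0.10 | 0.80 | 4.32 | 99% |

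The gap is assumed, so it was varied. At 6 years the last column becomes 10% / 36% / 89%; at 5 years, 8% / 27% / 76%.

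**Simulation with other assumptions.** Ages uniform on 0.5–6 and 6–18 years, 62 versus 55 children, no disease difference, 1000 runs per scenario, age trend linear or logarithmic.

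- Unadjusted comparison: rejection about 5% with no trend, 54–75% with a total trend of 1 SD from 0.5 to 18 years, and 98–100% with 2 SD.
- With a linear age term: rejection about 4–6%. The group–age correlation is 0.857, so the variance inflation factor is 1/(1 − 0.857²) = 3.77 and the SE grows by about √3.77 = 1.9 (0.19 to about 0.36 SD). A bias of 0.04–0.10 SD remains when the true trend is logarithmic.
- Difference of deviations, (asthmatics − their controls) − (wheezers − their controls): rejection about 4–6% in every scenario. SE is 0.31–0.35 SD with 59 paediatric controls and 0.40–0.43 SD with 30.

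**Cost in precision.** SE of the difference of deviations = √(1/62 + 1/55 + 2/m), with m healthy children per band.

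- m = 25: √(0.03431 + 0.08) = 0.338; ratio to the direct contrast 0.338/0.185 = 1.83.
- m = 15: √(0.03431 + 0.1333) = 0.409; ratio 2.21.

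**The case against.** **Adjustment is possible.** A reader might infer that disease and age are perfectly confounded and that age adjustment is impossible. The documents do not support this. Age varies within each group, so group and age are not collinear, and a linear age term restored the error rate in the simulation. What stands is narrower: matching is impossible, and adjustment depends on a model for the age trend that cannot be checked across the cut.

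**No specific test is fixed.** The aim speaks of similarities, the sentence on tests does not name its two groups, and model terms are commonly left to a fuller plan. That is fair, and the missing age term is not the point. The point is a claim made without an age caveat about groups whose definitions exclude overlap. No analysis plan can create that overlap.

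**Within-child change helps.** Each child has two follow-up visits, with blood at baseline and the second follow-up. Change within a child removes stable age-level differences, so the calculation above applies only to cross-sectional levels. The response itself may still depend on age, and the article does not restrict the wheezer–asthmatic comparison to change.

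**The split is largely clinical.** Comparing preschool wheeze with school-age asthma necessarily crosses ages. That explains the confounding but does not remove it.

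**Two side points carry little weight.** The strict inequalities put a child aged exactly 6 in neither band, and the gestational-age rule ("a gestational age over 37 weeks with an inconspicuous peripartal/postnatal period") is written for asthmatics only. A reader might infer a further bias from these, but the first may be shorthand and the article shows no effect of either.

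**Conclusion.** The concern holds for the direct wheezer–asthmatic comparison. The absence of age overlap rests on the article alone. The size does not: the 14% / 57% / 99% figures depend on an assumed 8-year gap and assumed slopes, and fall with a smaller gap.

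It would go too far to conclude that the cohort cannot address the question. The planned age-matched healthy children allow an indirect comparison, although the article does not tie them to this contrast. That route assumes that normal ageing is alike in healthy and diseased children. Even when it works, it cannot tell two different diseases from one disease expressed differently by age.

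Severity: should-fix. This is an exploratory observational cohort, and the remedy is a caveat and a better-anchored contrast.

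**What to change.** 1. Beside the claim in Advantages and Pitfalls, state that direct differences between wheezers and asthmatics cannot be attributed to disease rather than age.
2. Base this inference on each diseased group's deviation from its age- and sex-matched healthy children. Compare the two deviations between age bands, with continuous age and sex in the model.
3. State the assumption that normal ageing is alike in healthy and diseased children.
4. Call a marker shared only if it deviates from matched controls in the same direction in both bands, and report a confidence interval for the difference of deviations. A non-significant interaction is not evidence that a marker is shared.
5. Report how many of the 59 healthy participants are children, by age band.

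**Cost.** The changes are to wording and analysis and use controls already planned. The price is the precision loss calculated above. Whether the current controls suffice cannot be judged until their paediatric share is known; if it is small, more healthy children may be needed.

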Then, cytokine and chemokine analyses in different biomaterials, e.g., serum, plasma, and induced sputum, will show whether an acute exacerbation is associated with specific “cytokiome” levels and whether their release can be used as potential laboratory exacerbation parameter in clinical routine. The additional biomaterials, particularly sera/plasma and cells obtained from the study cohort, may support the idea of translational research to establish biomarkers for early diagnosis of exacerbation and rapid treatment to reduce morbidity and mortality. The experimental results will be compared by correlation analyses with the clinical item parameters obtained from the questionnaires. The listed network partners (including life scientists and physicians) are clinically and experimentally experts in their area, and the methods are appropriated to implement these research questions into praxis. Most of the described projects have been done or will be performed soon.

In summary, the main focus of our clinical and experimental work is to detect new phenotypes and endotypes, evaluate developed biomarkers and to identify new biomarkers, to uncover the functions of individual cells during an exacerbation, and to decipher the characterization of the microbiome and its role during exacerbation.

Due to the significance of this extraordinary study design and population and the currently performing analyses on the biomaterials with the emphasis on different clinical and molecular levels will present comprehensive insights into the molecular “barcodes of asthma,” which might contribute to improving our understanding of relevant common and individual pathomechanisms, and as such may serve as a highly relevant example for implementation the idea “from patient to bench and from the bench back to the children's hospital” to provide a potential clinical and therapeutic translation.

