All analyzed biomaterials and data involving human participants are in accordance with ethical standards and with the Helsinki declaration (1964) and its later amendments or comparable ethical standards. Ethical approval and later amendment approvals are obtained by the Ethics Committees of Witten/Herdecke University and Ärztekammer Nordrhein, and the study is registered at the German Clinical Trials Register (DRKS). All experiments, including the data extraction and analyses, were and will be obtained pseudonymously. The obtained subject-relevant information and biomaterials were and will be separately coded with study-relevant numbers and codes. All subject-relevant data and experimental results will be filled in a database to perform correlation analyses. With this coding strategy, except the (deputy) study head, nobody may follow retrospectively to patient-sensitive information. All biomaterials were processed according to established internal standard operating procedures and were stored at −80°C or in liquid nitrogen until experimental use. The study recruitment is still ongoing, and the current subject and biomaterial numbers allow first pilot experiments and statistical analyses. The description of the collected data will be done on the basis of statistical parameters. Insofar as the distribution of the data enables, the comparison of the two groups will be carried out using analyses of variance and typical significance tests. Data will be presented as box plots with medians, interquartile ranges, minimum–maximum values or standard deviation, or standard error of the mean. In addition, the data will be presented and analyzed by heat maps, cluster analyses, point clouds, bar, and column charts. Moreover, sequencing results will be normalized within each group, and normalization methods, e.g., DeSeq2, will be performed as previously described by Anders and Huber (33). In addition, metagenomic and proteomic data will be analyzed by professional biostatisticians within our study network. The raw data will be uploaded on separate repository databases, as stated by the journal's requirements. For the experiments, age- and sex-matched stratification will be done between diseased and healthy groups in which each diseased patient will be compared with the same healthy children based on age and sex.

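### The patient-control comparability rule covers age and sex only; with two recruiting hospitals and different recruitment routes, nothing stated keeps the hospital mix equal, so a hospital difference can appear as a disease effect.

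*Protocol article*

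**What the plan says.** All places are in the protocol article.

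- **Matching.** Methods and Analysis, in the paragraph on inclusion criteria, states: "The healthy pediatric controls will be age- and sex-matched with diseased children (preschool asthmatics/wheezers and asthmatics". The statistics paragraph later in that section repeats the rule: "For the experiments, age- and sex-matched stratification will be done between diseased and healthy groups", and adds that "each diseased patient will be compared with the same healthy children based on age and sex". No other matching or stratification factor between patients and controls is named.
- **Hospitals.** Methods and Analysis, after the questionnaire table, lists two participating centers: a university hospital and a teaching hospital. Advantages and Pitfalls confirms this: "This study is a prospective, multicenter, and observational cohort study conducted in two centers in Germany".
- **Network.** Advantages and Pitfalls also says, among the study's strengths: "The large study network from a total of 12 centers offers valid feasibility of the experiments".
- **Recruitment routes.** The same part of Methods and Analysis says that patients present at the emergency room. Controls are mostly children of staff at the study centers, with social platforms, flyers, newspapers and similar calls as alternatives.
- **Handling.** The statistics paragraph and Advantages and Pitfalls both refer to standard operating procedures for processing biomaterials.
- **Numbers.** Methods and Analysis gives 62 wheezers, 55 asthmatics and 59 healthy subjects, the last group including adults. Neither patients nor controls are broken down by hospital.

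**The concern.** Matching on age and sex balances age and sex. It does not balance the hospital through which a subject entered. Emergency-room attendance and recruitment among staff families or by public call are separate processes, and each can split differently between the two hospitals.

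The outcomes include small RNAs, cytokines and the airway microbiome. Catchment, case mix, local flora and early sample handling are plausible sources of a difference between hospitals in such readouts. If there is a difference and the groups have unequal hospital mixes, an unadjusted patient-control contrast carries part of it. A candidate biomarker could then reflect where subjects were recruited rather than the disease.

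**Working it through.** **1. Reproduce the article's count.** 62 + 55 + 59 = 176, as stated. Patients: 62 + 55 = 117. Healthy subjects: 59. The article gives no significance level, power or effect size to check.

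**2. Inputs.** The group sizes are from Methods and Analysis. Three inputs are assumptions, because the article gives none of them: a two-sided 5% level, the imbalance in hospital mix, and the shift between hospitals in SD units of the outcome.

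**3. Bias.** Let *D* be the share of patients recruited at hospital A minus the share of controls recruited there, and *s* the hospital shift in SD. Without adjustment:

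bias = *D* × *s*

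The bias is zero if either *D* or *s* is zero.

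**4. False-positive rate when there is no disease effect.**

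SE = √(1/117 + 1/59) = 0.160 SD

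rate = P(Z > 1.96 − bias/SE) + P(Z < −1.96 − bias/SE)

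- *D* = 0, any *s*: bias 0; rate 5.0%.
- *D* = 0.10, *s* = 0.5: bias 0.05; bias/SE = 0.313; rate = 0.0498 + 0.0115 = 6.1%.
- *D* = 0.30, *s* = 0.5: bias 0.15; bias/SE = 0.939; rate = 0.1537 + 0.0019 = 15.6%.

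The range for other assumed shifts:

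| Imbalance *D* | *s* = 0.2 | *s* = 0.5 | *s* = 0.8 |
|---|---|---|---|
| 0.10 | 5.2% | 6.1% | 7.9% |
| 0.30 | 6.6% | 15.6% | 32.4% |

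**5. Sensitivity to the contrast.** Step 4 pools the two disease groups and uses all 59 healthy subjects, including adults. Taking each disease group alone against the 59, with *s* = 0.5:

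- 62 wheezers: SE = √(1/62 + 1/59) = 0.182; rate 5.9% at *D* = 0.10 and 13.1% at *D* = 0.30.
- 55 asthmatics: SE = √(1/55 + 1/59) = 0.187; rate 5.8% and 12.6%.

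Restricting to pediatric controls would raise the SE and lower these rates further. For the same *D* and *s*, the bias itself does not change.

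**6. Precision cost of adjusting.** Suppose 65% of patients and 35% of controls come from hospital A (an assumed split with *D* = 0.30).

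- Overall share at A: (117 × 0.65 + 59 × 0.35)/176 = 0.549.
- Squared correlation of group with hospital: 0.30² × (117/176)(59/176) / (0.549 × 0.451) = 0.081.
- The SE of the group contrast is multiplied by √(1/(1 − 0.081)) = 1.043, an increase of about 4%.

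**The case against.** **No imbalance and no hospital shift are shown.** Bias needs both. Controls come mostly from staff families of the study centers, in the plural, so the main control source is tied to the same hospitals that supply patients, and the mix may be balanced. This stands: the point is a risk left open, not a demonstrated bias.

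**The operating procedures already address handling.** They do, and materials were tested before recruitment. The article also does not say where samples are processed, so a handling difference between hospitals cannot be presumed. But uniform procedures do not equalize case mix, catchment or local flora.

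**A condensed article may leave model terms to the full protocol or analysis plan.** This also stands, and the absence of a hospital term in the analysis text is not in itself the point. The article does, however, state its comparability rule explicitly, twice, and names only age and sex.

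**The 12 centers.** A reader might infer that the 12-center sentence contradicts the two recruiting hospitals, or that it overstates how far results generalize. The text supports neither reading. That sentence is about feasibility of the experiments, and Aims and Scopes describes the partners in these terms: "The listed network partners (including life scientists and physicians) are clinically and experimentally experts in their area". Advantages and Pitfalls openly lists the regional limitation: "Our study cohort will be recruited in two urban centers, and a comparison cohort living in rural areas is currently not included". The term for the network is used loosely, but this is a matter of wording and does not affect any result.

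**Conclusion.** The point holds as a gap in the stated comparability rule. Age and sex matching does not protect the patient-control contrast against a hospital difference, and the two groups are recruited by different routes.

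The size cannot be derived from the article. It is zero with a balanced hospital mix. With an assumed 0.5 SD shift in the pooled comparison, the false-positive rate is about 6% at a 10-point imbalance and about 16% at 30 points; against single disease groups the latter is about 13%. A reader might infer that hospital differences do distort the results. The documents do not support that, because they report neither hospital counts nor any difference between the hospitals.

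**What to change.** In the statistics paragraph of Methods and Analysis, keep the age and sex matching and add that recruiting hospital enters the patient-control comparisons as a fixed effect or stratum. Report the numbers of patients and controls by hospital, which also shows whether both hospitals supply both groups. If one group came entirely from one hospital, adjustment could not separate hospital from disease, and the report should say so.

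The cost is one degree of freedom per model and some precision if the mix is very unequal (about 4% on the SE in the assumed 65% against 35% split). Recruiting hospital should be known for every subject, so no new data are needed. Exact matching on hospital is not required, because it would shrink an already small control pool. Stating what the 12 network centers do is an optional wording change.
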